#### Secondary outcome

(1) Clinical symptoms: after confirming that the patients meet the inclusion criteria, researchers will ask about and record the clinical symptoms of the patients (including the duration of angina pectoris, frequency of weekly attacks, and the dosage of nitroglycerin) at baseline, weeks 4 and 8, and months 3 and 6 after enrollment.(2) Stopping rate of nitroglycerin: This will be recorded at the baseline and at weeks 4 and 8 and months 3 and 6 after enrollment.① Significant effect: discontinuation of nitroglycerin after treatment;② Effective: the dosage of nitroglycerin after treatment is >50% less than that before treatment;③ Ineffective: after treatment, the dosage of nitroglycerin decreased by <50% or increased, compared with that before treatment.(3) SAQ: This is a 19-item self-administered questionnaire measuring five dimensions of coronary artery disease: physical limitation (question 1), anginal stability (question 2), anginal frequency (question 3–4), treatment satisfaction (question 5–8), and disease perception (question 9–11) (28). The 19 items will be scored individually to obtain the total SAQ score, which is transformed into a standard score according to this formula: Standard score = (actual score – lowest score of the dimension) x100/(highest score of the dimension – lowest score of the dimension). Patients' quality of life and body function are proportional to the score, which will be recorded at the baseline and weeks 4 and 8 and months 3 and 6 after enrollment.(4) SF-36: The MOS item short will be used from the health survey (SF-36) to assess patients' quality of life. As a concise health questionnaire, SF-36 comprehensively summarizes the quality of life of the subjects from eight aspects: Physical Functioning (PF), Role-Physical (PR), Bodily Pain (BP), General Health (GH), Vitality (VT), Social Functioning (SF), Role-Emotional (RE), and Mental Health (MH). There are 36 questions, and the quality of life is proportional to the score (29). SF-36 is effective in detecting the health perception of the general population, easy to use, and highly accepted by patients, and studies have proven it to be a promising tool due to its high reliability (30, 31). SF-36 will be recorded at baseline, weeks 4 and 8, and months 3 and 6.

$$\begin{array}{l} \begin{array}{c} \text{PF}=(\text{Actual score}-\;20)/40\times 100;\\ \text{PR}=(\text{Actual score }-4)/4/4\times 100\\ \beta \text{P}=(\text{Actual score}-2)/10\times 100;\\ \text{GH}=(\text{Actual score}-5)/20\times 100\\ \text{VT}=(\text{Actual score}-4)/20\times 100;\\ \text{SF}=(\text{Actual score}-2)/8\times 100\\ \text{R}\epsilon =(\text{Actual score}-3)/3\times 100;\\ \text{MH}=(\text{Actual score}-5)/25\times 100 \end{array} \end{array}$$

(5) ECG: This will be recorded at baseline and after the intervention. Routine 12-lead ECG will performed with the patient at rest. The evaluation of the standard curative effect of ECG is based on the curative effect standard of coronary heart disease and angina pectoris (32) (Table 4).(6) Serum lipids: Venous blood samples (5 mL) will be collected before and 8 weeks after intervention. After coagulation, samples will undergo centrifugation at 3,000 r/min. The supernatant will be collected after 15 min and serum lipid levels (triglycerides, cholesterol, low-density lipoprotein cholesterol, high-density lipoprotein cholesterol, lipoprotein-a, small, dense low-density lipoprotein cholesterol) will be determined using enzyme-linked immunosorbent assay (ELISA). (7) Hs-CRP: Venous blood samples (5 mL) will be collected before and 8 weeks after intervention. After coagulation, the serum will be centrifuged at 2,000 r/min for 20 min, and the CRP level will detected quantitatively using ELISA.(8) The TCM syndrome scores of patients will be recorded at the baseline and at weeks 4 and 8 and months 3 and 6 after enrollment. TCM syndrome score indexes for patient evaluation includes chest pain, chest tightness and shortness of breath, palpitation, and fatigue. Each index is allotted 1–3 points, and the total score is 12 points. A higher TCM score suggests a more serious condition (33).(9) Intestinal flora: The feces were collected by the patients at home (at the baseline and the eighth week), the researchers distributed a sterile collection tube containing the preservation solution and a sterile spoon to the patients, and explained in detail to the patients how to collect the feces. After defecation, the patient uses a sterile spoon to collect from the inside of the stool and put it in the collection tube. Each patient keeps two specimens, each of which is about 1 g. The researchers then recycled the feces at −80°C for storage. High-throughput 16SrRNA sequencing will be used to effectively identify microbial species (including eight phyla: *Firmicutes, Bacteroidetes, Verrucomicrobia, Spirochaetae, Proteobacteria, Cyanobacteria, Saccharibacteria*, and *Synergistetes*) and their abundance in a particular environment. The significant differences in intestinal microecological composition and distribution abundance will be compared between the two groups, before and after treatment. The metabolic genes related to intestinal flora will be detected using macrogenomic sequencing, and the differences in KEGG metabolic pathway and species function will be predicted and analyzed.(10) Metabolomics: Fasting blood samples will be drawn at baseline and at the eighth week, and the fresh whole blood samples will be immediately sent to the laboratory under cold storage (ice-box transfer) and centrifuged at 4°C, at 3,000 r/min for 10 min. Finally, the supernatant (plasma) will be frozen at −80°C. The TMAO content will be determined using high-performance liquid chromatography–tandem mass spectrometry (HPLC-MS), and a standard curve will be drawn to calculate the serum TMAO concentration in patients with SAP. Non-targeted liposome detection, data preprocessing and database search, differential metabolite analysis, and bioinformatics analyses will be conducted using HPLC-MS.

**Table 4 T4:** Efficacy criteria of electrocardiogram.

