**Objective:**

To determine the effect of Baduanjin exercise on the symptoms of patients with SAP and the intestinal flora, explore the action links and targets of Baduanjin intervention in elderly patients with SAP, and explain its mechanism.

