### Statistical analysis

A full-analysis set (FAS), per-protocol analysis set (PPS), and safety analysis set (SAS) will be created according to the principle of intentional therapy (34). FAS participants are identified as those who received at least one exercise. Those who adhere to the treatment plan but changed groups midway are part of the PPS. For safety indicator assessment, researchers will use the SAS to analyze the incidence of adverse events and laboratory indicators. Statistical analysis will be conducted by third-party statisticians blinded to experimental grouping and intervention methods, using SPSS 25. We will analyze the baseline demographic data to determine the comparability between the two groups. Mean ± standard deviation will be used for continuous variables that conform to normal distribution, and median and quartile methods will be used for continuous variables that do not conform to normal distribution. The Chi-square test or Fisher's exact test will be used to compare classified counting data. The paired *t*-test will be used to compare differences within the group, and the independent-sample *t*-test will be used to compare differences between groups. If the data do not conform to normal distribution, a Wilcoxon paired test and Mann-Whitney U test will be used to analyze intra- or inter-group differences. *P* < 0.05 is considered as statistically significant.

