In conclusion, this experiment will confirm whether Baduanjin can be used as an adjuvant therapy for SAP. This randomized controlled trial will help to provide evidence to verify whether the mechanism of Baduanjin improving SAP is related to gut microflora.

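### The single P<0.05 rule, with unranked within-group and between-group tests, makes no exception for the flora, KEGG and lipid outcomes that serve the mechanism objective

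*Protocol article*

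**What the plan says.** All references are to the protocol article.

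- **Aim.** The Objective in the Abstract is partly to "explore the action links and targets of Baduanjin intervention in elderly patients with SAP, and explain its mechanism". The closing paragraph of the Discussion says the trial will help to "provide evidence to verify whether the mechanism of Baduanjin improving SAP is related to gut microflora".
- **Outcomes.** Secondary outcome, items (9) and (10), covers 16S sequencing that "will be used to effectively identify microbial species (including eight phyla", which are then named one by one. It adds metagenomic sequencing, where "the differences in KEGG metabolic pathway and species function will be predicted and analyzed", serum TMAO, and a lipid workflow: "Non-targeted liposome detection, data preprocessing and database search, differential metabolite analysis, and bioinformatics analyses will be conducted using HPLC-MS". For the flora, "The significant differences in intestinal microecological composition and distribution abundance will be compared between the two groups, before and after treatment". No taxon, diversity index, pathway, lipid or single contrast is marked as the one that decides. These outcomes stand among the other secondary outcomes and are not called exploratory.
- **Decision rule.** The Statistical analysis section names paired and independent t-tests, with non-parametric versions: "a Wilcoxon paired test and Mann-Whitney U test will be used to analyze intra- or inter-group differences". The threshold is P "< 0.05 is considered as statistically significant". It does not say which type of test carries the inference, and it sets no outcome apart.

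**The concern.** There are two separate problems.

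1. **Number of tests.** A threshold suited to one comparison is stated for a set that contains at least eight phyla and TMAO, plus an unstated number of pathways and lipids. Some features can be declared different between arms when Baduanjin does nothing to flora or metabolites beyond what free exercise does.

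2. **Type of test.** A paired P<0.05 inside the Baduanjin arm counts as significant on the same footing as a between-group result. Both arms are prescribed moderate-intensity exercise 3–5 times a week for 8 weeks (Design; Intervention). The Introduction says that short-term endurance exercise improves the richness of the flora, and the Discussion says that exercise raises faecal short-chain fatty acids. By the article's own reasoning, a before/after change in the Baduanjin arm may come from exercise in general.

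At stake is the mechanism part of the objective. The efficacy conclusion on the primary outcome is not affected.

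**Working it through.** The article states no error rate, number of tests or sample size for these outcomes, so there is no figure of its own to reproduce.

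**Inputs from the article:** threshold 0.05; 8 named phyla; TMAO as one further targeted measure (8 + 1 = 9 tests); flora and TMAO measured at weeks 0 and 8 (Outcome measurements, Table 1); 90 patients per group with 20% loss allowed (Sample size), so 90 × 0.8 = 72 completers per arm.

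**Assumed, because the article does not give them:** the correlation between test statistics, 0 to 0.8; 100 KEGG and lipid features as an illustration; for step 3, a baseline-to-week-8 correlation of 0.5 and a common drift of 0.2 SD.

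**Step 1. One between-group contrast, no true difference.**
For m independent tests, P(at least one false positive) = 1 − 0.95^m, and the expected number is 0.05 × m. For correlated tests I took equally correlated normal statistics and integrated over the shared component.

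| m | independent | correlation 0.5 | correlation 0.8 | expected false positives |
|---|---|---|---|---|
| 8 (phyla) | 1 − 0.95^8 = 33.7% | 25% | 16% | 0.40 |
| 9 (phyla + TMAO) | 1 − 0.95^9 = 37.0% | 27% | 17% | 0.45 |
| 100 (assumed) | 1 − 0.95^100 = 99.4% | 78% | 36% | 5 |

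On the article's own count the rate is therefore about 3 times (16/5) to 7 times (37/5) the nominal 5%. The third row rests on an assumed count.

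**Step 2. Adding the within-group tests, no true change anywhere.**
Eight phyla with three contrasts each (between groups, within Baduanjin, within control) make 24 tests: 1 − 0.95^24 = 70.8% if independent. The three contrasts share data; simulating them with 72 per arm gave 68.9%.

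**Step 3. Both arms drift equally, no treatment effect.**
With a baseline-to-week-8 correlation of 0.5, the SD of the change is √(2 − 2 × 0.5) = 1. A drift of 0.2 SD then gives a paired non-centrality of 0.2 × √72 = 1.70, hence a power of about 0.39 for each feature.

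- At least one significant change among 8 features within the Baduanjin arm: 1 − 0.61^8 ≈ 98%.
- At least one significant result from either the between-group or the Baduanjin within-group tests: roughly 1 − (0.61 × 0.95)^8 ≈ 98.7%. Simulation of 2,000 trials agreed.
- Between-group tests alone, same simulation: 33.6%.

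The drift cancels in the between-group contrast and does not cancel in the paired one.

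**Step 4. After the change.**
A false-discovery procedure at 5% holds the chance of any false positive within a family at 5% when all its nulls are true. Across phyla, pathways and lipids, with TMAO as a single test, the overall chance is 1 − 0.95^4 = 18.5% if independent, however many features each family contains. One contrast named in advance is tested at 5%.

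**The case against.** The strongest reply is that this is a condensed article. Multiplicity rules for omics data commonly sit in the analysis plan or a bioinformatics plan, neither of which is shown, so the missing adjustment does not prove that none is planned. The Statistical analysis paragraph is generic and mentions neither KEGG nor lipids. An adjusted P value can also be read against 0.05. The flora sentence can be read as a between-group comparison at both sampling times. All of these outcomes are secondary.

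Much of this stands. Applying P<0.05 to the KEGG and lipid workflows is an inference from general wording, and silence about false-discovery control would not be a finding in itself. But the article is not merely silent. It prints one threshold and one set of tests without exception, and gives within-group tests equal standing. An unseen plan may correct that; the published rule still needs the correction.

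Three stronger readings are tempting, and the article does not support them:

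- **That a positive mechanism result is close to guaranteed by chance.** The named tests give about 16% to 37%. Near-certainty needs an assumed feature count or the within-group route with an assumed drift; even 100 features at correlation 0.8 give only 36%.
- **That the procedure cannot return a negative answer.** On the nine named between-group tests, there is a 63% to 83% chance of no false positive at all. Nor does the article say that one significant feature would count as success.
- **That the trial claims it will verify the mechanism.** The Discussion speaks only of helping to provide evidence on whether the mechanism is related to flora, and much of the surrounding language is exploratory.

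**Conclusion.** The point holds in a limited form. The stated rule is badly fixed for the flora and metabolite outcomes: a single threshold, no ranking of within-group against between-group tests, and a mechanism aim that depends on the results.

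The firm part of the size is the article's own count: about 34–37% for at least one false positive if independent, falling to about 16–17% at correlation 0.8. This assumes one between-group contrast per feature, no true differences, and the general threshold applied to each. The rise from KEGG and lipid features is likely, but its amount is unknown because their number is not given.

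The within-group problem needs no feature count. Both arms exercise, so a paired result in one arm does not bear on a Baduanjin-specific mechanism. The 98.7% only illustrates this and depends on the assumed 0.2 SD drift.

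**What to change.** In the Statistical analysis section, add a short paragraph for the flora and metabolite outcomes:

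1. Base inference on the between-group contrast only, and report within-group changes descriptively.
2. Control the false-discovery rate at 5% (for example by Benjamini-Hochberg) within each feature family: phyla and other taxa, KEGG pathways, lipids.
3. Describe feature-level results as exploratory, and bring the mechanism wording in the Objective and the closing paragraph of the Discussion into line with that.

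Optionally, name one between-group mechanistic contrast in advance, to be tested at two-sided 0.05. The week-8 TMAO difference or one overall test of community composition would serve, but the choice is the sponsor's. If an analysis plan already contains such rules, a sentence pointing to them is enough.

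The cost is wording and a little analysis work, with no new patients, samples or visits. The downside is that fewer individual taxa or lipids will be called significant. Recruitment has started (Trial status), so the change should be dated and made before anyone sees results by group.

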**Efficacy criteria of electrocardiogram**	
Significant effect	ECG returns to roughly normal or normal range of electrocardiogram.
Effective	After treatment, the ST segment rises ≥0.05 mv, but does not reach the normal level, the main lead causes the T waves to become shallow >25%, or the T wave changes from flat to upright; severe arrhythmia is improved.
Invalid	ECG is roughly the same as before.
Aggravation	The ST segment decreased more than 0.05 mV after treatment. In the main ECG leads, T wave changes more deeply (up to 25%); or T wave changes from upright to flat, or upright T wave inversion, ectopic rhythm, atrioventricular or ventricular block.

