#### Exclusion criteria

The exclusion criteria are the following:

(1) Severe arrhythmia and moderate cardiac insufficiency (EF <40%);(2) Uncontrolled hypertension, systolic blood pressure (SBP) ≥180 mmHg, and diastolic blood pressure (DBP) ≥100 mmHg;(3) Three-month recent history of AMI or PCI, coronary artery bypass grafting, severe trauma, and cerebrovascular accident;(4) Severe shock and primary organ diseases (such as of the liver, kidney, lung, etc.);(5) Obvious infection, fever, and severe anemia;(6) Severe joint disease;(7) Antibiotic use or participation in any antibiotic, probiotic, or laxative research in the 3 months preceding the study;(8) Gastrointestinal diseases such as diarrhea and ulcerative colitis in the past 2 months.

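### Table 4's ECG grades are neither mutually exclusive nor exhaustive: the T-wave worsening bound is a ceiling, normal baseline tracings have no rule, and one route to *Effective* conflicts with an exclusion

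*Protocol article*

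**What the plan says.** The ECG is a secondary outcome, recorded at weeks 0 and 8. The Secondary outcome section, item 5, states "Routine 12-lead ECG will performed with the patient at rest" and sends the reader to Table 4, which it bases on a cited standard. Table 4 has four grades:

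- *Significant effect*: "ECG returns to roughly normal or normal range of electrocardiogram".
- *Effective*: an ST rise of at least 0.05 mV that stops short of normal, or "the main lead causes the T waves to become shallow >25%, or the T wave changes from flat to upright; severe arrhythmia is improved".
- Unchanged tracings, graded *Invalid*: "ECG is roughly the same as before".
- *Aggravation*: an ST fall of more than 0.05 mV, or, in the main leads, "T wave changes more deeply (up to 25%); or T wave changes from upright to flat", or T-wave inversion, ectopic rhythm or block.

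The inclusion criteria are a stable angina diagnosis, age 60 to 80, severity grade I to III, and consent. The first exclusion criterion opens "Severe arrhythmia and moderate cardiac insufficiency (EF <40" (the ejection-fraction limit is a percentage). The article names the outcome only as ECG changes. The one effective rate for which it gives a formula, under Table 3, is for angina symptoms.

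**The concern.** A graded outcome needs rules that place each patient in exactly one grade, and in a grade that makes clinical sense. Three features of Table 4 work against this. The T-wave bound for worsening is an upper limit where a lower one would be expected. Patients whose resting ECG is normal at entry are not provided for. One route to *Effective* describes a condition that should keep a patient out of the trial.

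At stake is the meaning of the ECG result. Marked T-wave worsening could miss the worst grade while trivial change enters it, and patients who cannot improve could be counted as failures or as top responders. The Trial status section says that recruitment has begun, so the rules should be settled before tracings are graded.

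**Working it through.** The protocol states no figure for the ECG outcome, so there is none to reproduce. The check sets the rules side by side, followed by one illustration on assumed rates.

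**1. T-wave bound.** Take a patient whose only change is a deeper T wave in a main lead.

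| Deepening | *Aggravation* (at most 25%) | *Invalid* (roughly unchanged) |
|---|---|---|
| 1% | met | met |
| 26% | deepening rule not met | not a natural fit |

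The first row is an overlap and the second a gap. *Effective* uses more than 25% as a minimum, so the two directions do not mirror each other.

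**2. Normal at both visits.** None of the four inclusion criteria asks for an abnormal resting ECG, and no exclusion removes normal tracings. In Table 4, the top grade speaks of an ECG that returns to normal, which presupposes an abnormal start. A tracing normal at weeks 0 and 8 has not returned; it is unchanged, so literally *Invalid*. Only if the top row is read by end state alone does it become *Significant effect*.

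To see the effect on a rate that adds *Significant effect* and *Effective*, let *s* be the share normal at both visits, equal in the two arms, and let *a* and *b* be the proportions improving among the remaining patients.

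- Filed as *Invalid*: rates (1 − s)a and (1 − s)b; difference (1 − s)(a − b).
- Filed as *Significant effect*: rates s + (1 − s)a and s + (1 − s)b; difference again (1 − s)(a − b).
- Abnormal at baseline only: rates a and b; difference a − b, on 90(1 − s) patients per arm.

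The planned 90 per arm comes from the Sample size section. The values a = 50%, b = 30% and all values of *s* are assumptions. Power is for a two-sided 5% comparison of two proportions, without dropout.

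| s | Filed *Invalid* | Filed *Significant effect* | Difference, either filing | Power: *Invalid* / *Significant effect* / abnormal only |
|---|---|---|---|---|
| 0.1 | 45% v 27% | 55% v 37% | 18 points | 71 / 68 / 74% |
| 0.3 | 35% v 21% | 65% v 51% | 14 points | 55 / 48 / 63% |
| 0.5 | 25% v 15% | 75% v 65% | 10 points | 39 / 31 / 49% |
| 0.7 | 15% v 9% | 85% v 79% | 6 points | 23 / 18 / 32% |

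The choice of filing moves each arm's rate by exactly *s* but leaves the difference between arms unchanged. What it costs against the abnormal-only comparison, where the difference stays at 20 points, is dilution by the factor 1 − s. In this illustration, restricting to abnormal baselines gives higher power than either filing, despite fewer patients.

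**3. Arrhythmia.** *Effective* is also reached when "severe arrhythmia is improved". Improvement from baseline needs severe arrhythmia at baseline, which the first exclusion criterion should prevent.

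**The case against.** The strongest reply is that little of this disturbs the comparison between arms. The word for returning to normal, together with the *Effective* row's condition that the ST segment stays short of normal, shows that the scale measures movement back from an abnormal start. A reader might infer that a normal-to-normal patient falls into two grades at once; the text does not force that. A reader might also infer that an ECG effective rate is left without a value. The article defines no such rate, and the four grades can be compared with the chi-square or Fisher test named under Statistical analysis. Both replies stand. What they leave is that the literal grade counts an unimprovable patient as a non-responder.

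It is also fair that a shift of tens of points in one arm is only the assumed share restated, and that it cancels in the difference when the share is balanced and the filing is the same in both arms. That stands too. The dilution and the uninterpretable absolute rates remain.

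A route to *Effective* that nobody meets misgrades nobody. This makes the arrhythmia item a contradiction to reconcile rather than a source of bias. If the first exclusion is read as requiring both conditions together, even the contradiction weakens, although a list of separate conditions is the more natural reading.

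Complaints about the ST rules do not carry. The mismatch at exactly 0.05 mV is trivial, and stopping short of normal already implies a baseline below normal.

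Finally, the T-wave bound may be a translation slip, and the cited standard is not at hand. That limits what can be said about the intended threshold. It does not rescue the rule as printed.

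**Conclusion.** The concern holds in this form: Table 4 as printed has grades that are neither mutually exclusive nor exhaustive. The T-wave bound is the clearest error, since following it grades trivial deepening as worsening and leaves deepening beyond 25% without a deepening rule. Normal baseline ECGs have no sensible place. With a balanced share they dilute the between-arm difference by the factor 1 − s and shift the absolute rates by an amount that depends on the filing. The documents do not give *s*, so the actual size is unknown and the table above is illustration only. The arrhythmia item conflicts with the exclusion criteria.

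A reader might go further and conclude that the ECG result would reflect reader habit rather than treatment. The documents do not support that, because under consistent filing and balanced shares the difference between arms is the same either way.

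The conclusion rests on the listed entry criteria. The diagnosis itself refers to an outside guideline that is not shown. The ECG is a secondary outcome, so the primary outcome and sample size are untouched.

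**What to change.** Before any ECG is graded:

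1. Make the T-wave deepening bound in *Aggravation* a minimum rather than a maximum, consistent with the 25% improvement threshold. Check the exact wording, including whether 25% itself counts, against the cited standard.
2. Grade improvement only in patients with an ST-T abnormality on the baseline tracing. Report patients with a normal baseline separately, as stayed normal or became abnormal.
3. Reconcile the arrhythmia item in *Effective* with the first exclusion criterion.

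These are wording changes plus one rule on the analysis population. No new data are needed, because the tracings at weeks 0 and 8 are already scheduled. The cost is that the improvement analysis rests on fewer patients, by a number that will be known once the baseline ECGs are read.
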